**107 Methods and timing for assessing, recording, and analyzing safety parameters**

As the safety profiles of both interventions (Nasovac-S and azithromycin) are well established and the study does not have defined safety endpoints, data on adverse events will be collected by passive follow up and questions asked during scheduled visits to the clinical trial site.

**108 Time windows for the collection of adverse event data**

All adverse events that occur through day 21 post-vaccination with Nasovac-S in groups A, B and D will be assessed and recorded (during scheduled visits at day 2, 7 and 21 after vaccination or if subjects present to the clinical trial site due to illness in between these visits). All adverse events occurring through Day 28 following administration of azithromycin (Group

D only) will be assessed and recorded (at the scheduled visit at day 28 after azithromycin or if subjects present to the clinical trial site due to illness before this visit). Parents/guardians will be advised to contact the study team via telephone or attend the clinical trial site if their child is unwell in between scheduled study visits.

Group C will receive Nasovac-S after NPS has been taken on the day 21 visit, so they are also afforded the same potential benefit of influenza vaccination by participating in the study as groups A, B and D. Given the existing safety data on Nasovac-S (Section 4.1.9), no extra visits will be scheduled for group C specifically for the purpose of gathering adverse event data. Parents/guardians will, however, be advised to contact the study team or bring their child to the health centre if they have any concerns and adverse event data collected, graded and investigated as per AEs in other groups detailed in this section. This will be particularly relevant for post-vaccine AEs for 7 days following vaccination, but aligns with the agreement to assess all study subjects if they are unwell until October 31st of the year of vaccination.

## **109 Solicited safety data**

All participants will be assessed for local and systemic reactions through 7 days post-vaccination with Nasovac-S. Using a standardized data collection instrument, the following local and systemic reactions will be documented and be graded on magnitude of reaction on the scheduled day 2 visit (for day 0 – 2 symptoms) and day 7 visit (for day 3 – 7 symptoms) following vaccination (see section 7.1.3).

### **Local reactions:**

- Cough
- Nasal discomfort
- Runny nose
- Sore throat
- Stuffy nose
- Ear pain

### **Systemic Reactions:**

- Chills
- Headache
- Vomiting
- Fever (measured)
- Irritability/Decreased Activity
- Muscle/Joint pain
- Tachypnea (measured respiratory rate)

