**Table S10. Adverse events between baseline (day 0) and day 7 of the study**

| Adverse event | LAIV
(n=213) | Control
(n=108) | P value |
|----------------------|-------------------------|----------------------------|----------------|
| Fever                | 32 (15.0%)              | 11 (10.2%)                 | 0.23           |
| Sore throat          | 1 (0.5%)                | 0 (0.0%)                   | 0.48           |
| Chills               | 1 (0.5%)                | 0 (0.0%)                   | 0.48           |
| Muscle/joint pains   | 0 (0.0%)                | 0 (0.0%)                   | -              |
| Headache             | 4 (1.9%)                | 0 (0.0%)                   | 0.15           |
| Epistaxis            | 0 (0.0%)                | 0 (0.0%)                   | -              |
| Nasal congestion     | 7 (3.3%)                | 1 (0.9%)                   | 0.20           |
| Reduced appetite     | 9 (4.2%)                | 8 (7.4%)                   | 0.23           |
| Rhinorrhoea          | 103 (48.4%)             | 25 (23.5%)                 | <0.0001        |
| Rash                 | 6 (2.8%)                | 4 (3.7%)                   | 0.67           |
| Dyspnoea             | 1 (0.5%)                | 0 (0.0%)                   | 0.48           |
| Cough                | 54 (25.4%)              | 19 (17.6%)                 | 0.12           |
| Sputum production    | 5 (2.3%)                | 2 (1.9%)                   | 0.77           |
| Irritability         | 0 (0.0%)                | 1 (0.9%)                   | 0.16           |
| Vomiting             | 8 (3.8%)                | 5 (4.6%)                   | 0.71           |
| Lethargy             | 5 (2.3%)                | 1 (0.9%)                   | 0.37           |
| Diarrhoea            | 13 (6.1%)               | 12 (11.1%)                 | 0.11           |
| Ear pain             | 4 (1.9%)                | 0 (0.0%)                   | 0.15           |

Data are n (%). P values were derived from Chi-square test or Fisher's exact test where appropriate. LAIV=live attenuated influenza vaccine.

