**Table S11. Adverse events between day 7 and day 21 of the study**

| Adverse event | LAIV
(n=213) | Control
(n=108) | P value |
|----------------------|-------------------------|----------------------------|----------------|
| Fever                | 39 (18.3%)              | 15 (13.9%)                 | 0.32           |
| Sore throat          | 3 (1.4%)                | 0 (0.0%)                   | 0.22           |
| Chills               | 0 (0.0%)                | 0 (0.0%)                   | -              |
| Muscle/joint pains   | 0 (0.0%)                | 0 (0.0%)                   | -              |
| Headache             | 4 (1.9%)                | 0 (0.0%)                   | 0.15           |
| Epistaxis            | 0 (0.0%)                | 0 (0.0%)                   | -              |
| Nasal congestion     | 4 (1.9%)                | 1 (0.9%)                   | 0.52           |
| Reduced appetite     | 9 (4.2%)                | 8 (7.4%)                   | 0.23           |
| Rhinorrhoea          | 108 (50.7%)             | 28 (25.9%)                 | <0.0001        |
| Rash                 | 4 (1.9%)                | 2 (1.9%)                   | 0.99           |
| Dyspnoea             | 1 (0.5%)                | 0 (0.0%)                   | 0.48           |
| Cough                | 76 (35.7%)              | 30 (27.8)                  | 0.16           |
| Sputum production    | 2 (0.9%)                | 1 (0.9%)                   | 0.99           |
| Irritability         | 0 (0.0%)                | 1 (0.9%)                   | 0.16           |
| Vomiting             | 4 (1.9%)                | 5 (4.6%)                   | 0.16           |
| Lethargy             | 3 (1.4%)                | 1 (0.9%)                   | 0.71           |
| Diarrhoea            | 14 (6.6%)               | 8 (7.4%)                   | 0.78           |
| Ear pain             | 3 (1.4%)                | 0 (0.0%)                   | 0.22           |

Data are n (%). P values were derived from Chi-square test or Fisher's exact test where appropriate. LAIV=live attenuated influenza vaccine.

[figure not shown]

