### **73 Clinical examination, vital sign and anthropometry**

A physical examination is performed by the investigator or sub-investigator with particular focus on the inclusion and exclusion criteria set out for the study. All relevant positive and negative findings will be documented within the subject's clinical notes and key findings will be captured in the CRF. Any abnormal finding requiring further treatment will be managed according to local practice or an appropriate referral made according to the nature of the finding.

A subject's axillary temperature will be recorded at each visit, using a calibrated thermometer. At the same time points the respiratory rate and heart rates will be measured.

Height and weight will be measured and recorded at each visit using appropriately calibrated equipment. Calculate Z-score (a z-score of less than -3 indicated severe protein-energy malnutrition and is an exclusion criterion).

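### Table S10 omits two of the 13 solicited reactions, measured tachypnoea and nasal discomfort, and neither Table S10 nor Table S11 shows the severity grades that the protocol requires

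*Combined protocol and SAP*

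**What the plan says.** The protocol section on solicited safety data (heading 109) says that "the following local and systemic reactions will be documented and be graded on magnitude of reaction on the scheduled day 2 visit" and again at the day 7 visit, over the first 7 days after Nasovac-S. Two lists follow. The local list has six items, one of which is "Nasal discomfort". The systemic list has seven, of which two are defined by a measurement: "Fever (measured)" and "Tachypnea (measured respiratory rate)".

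The section on assessment of severity (heading 106) requires all adverse events to be graded mild, moderate or severe, and gives numeric cut-offs for measured fever and measured tachypnoea. The section on unsolicited data (heading 111) repeats the grading requirement. On collection, the section on clinical examination and vital signs (heading 73) has temperature recorded at each visit and adds: "At the same time points the respiratory rate and heart rates will be measured".

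The appendix has two safety tables: S10, "Adverse events between baseline (day 0) and day 7 of the study", and S11, "Adverse events between day 7 and day 21 of the study". Each prints the same 18 event types as n (%) with a P value, for 213 LAIV and 108 control children. The appendix contents list no other adverse event table. The sections on safety methods (heading 107) and pause rules (heading 117) state that the study has no defined safety endpoints.

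**The concern.** Tachypnoea is the only solicited respiratory sign defined by measurement. The other respiratory items, and the dyspnoea row that S10 does print, are symptoms. Site staff know the allocation once the envelope is opened, and controls receive nothing until day 21, so a graded count of a measured sign would add something that symptom reports cannot. It is missing from the table that covers the solicited window.

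The grades matter for a second reason. Rhinorrhoea shows the clearest difference in either table. Without grades, a reader cannot tell a large excess of trivial runny noses from one that includes moderate or severe events. The protocol's own safety background for this vaccine is graded: the Senegal study gives mild, moderate and severe rates and counts tachypnoea among its systemic reactions, and the Bangladesh study separates moderate from mild events. S10 cannot be set beside either on those terms.

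**Working it through.** **Matching the solicited list to Table S10.** Runny nose is read as rhinorrhoea, stuffy nose as nasal congestion, and irritability/decreased activity as irritability.

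| Solicited item | Row in S10 |
|---|---|
| Cough, sore throat, ear pain | yes |
| Runny nose, stuffy nose | yes, as rhinorrhoea and nasal congestion |
| Nasal discomfort | **none** |
| Chills, headache, vomiting, fever, muscle/joint pain | yes |
| Irritability/decreased activity | yes, as irritability |
| Tachypnoea | **none** |

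Local 6 + systemic 7 = 13 items; 11 have a row; 2 of 13 (15%) do not.

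**Could the rows have been dropped for lack of events?** S10 prints muscle/joint pains and epistaxis as 0 v 0. S11 prints those two and chills as 0 v 0. Empty rows were therefore kept.

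**Grades.** Rows with a severity grade: 0 of 18 in S10 and 0 of 18 in S11.

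**Check that the tables were read correctly.** P values recomputed from the counts by chi-square without continuity correction agree with those printed. For example, fever in S10 (32/213 v 11/108) gives 0.229 against a printed 0.23, and cough (54/213 v 19/108) gives 0.117 against 0.12.

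**Rhinorrhoea, the difference that lacks grades.**
- S10: 103/213 = 48.4%; 25/108 = 23.1% (the table prints 23.5%); difference 25.2 percentage points.
- S11: 108/213 = 50.7%; 28/108 = 25.9%; difference 24.8 percentage points.

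**Precision of an added tachypnoea comparison.** The documents give no tachypnoea rate, so a common rate p in both arms is assumed. Half-width = 1.96 × sqrt[p(1 − p)(1/213 + 1/108)], with 1/213 + 1/108 = 0.01395.
- p = 0.02: 1.96 × sqrt(0.0196 × 0.01395) = 0.032
- p = 0.05: 1.96 × sqrt(0.0475 × 0.01395) = 0.050
- p = 0.10: 1.96 × sqrt(0.0900 × 0.01395) = 0.069

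As a guide to where in that range to look, the whole systemic composite in the Senegal study, tachypnoea included, adds up to 2.7 + 0.4 + 0.1 = 3.2% (LAIV) and 3.2 + 0.7 + 0.0 = 3.9% (placebo). A rate of 5% for tachypnoea alone would be above that composite.

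**The case against.** Several arguments limit the point, and most of them stand.

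- **The solicited window ends at day 7.** A reader might infer that S11 also fails to report 2 of 13 solicited items. It does lack those rows, but the reactions were not solicited between day 7 and day 21. The missing rows are a gap in S10 only; the missing grades are a gap in both tables, because all adverse events were to be graded.
- **No two-arm safety comparison was planned.** Solicited collection is tied to vaccination and to day 2 and day 7 visits. Table 1 of the protocol shows no day 2 procedures for controls, and the planned analyses contain no safety comparison. This limits the weight of the point. But S10 and S11 do compare the arms, with P values, on the other solicited items.
- **The additional rows are legitimate.** A reader might see epistaxis, rash, sputum production and diarrhoea as unplanned substitutes. They are unsolicited adverse events, which the protocol also set out to record.
- **Nasal discomfort may be inside another row**, such as nasal congestion or rhinorrhoea. The documents do not say; a footnote would settle it.
- **Control respiratory rates may not exist after enrolment.** The each-visit wording sits under screening and enrolment. The readable part of the study schedule, which covers group D only, lists respiratory rate under eligibility assessment alone. The fix has to allow for this.
- **A visit reading is not an interval count.** Day 7 and day 21 visits have +7-day windows, and a single reading gives prevalence at the visit. For this reason visit readings should not replace the fever rows, which count occurrence over the interval.

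The most tempting stronger reading is that the safety results were reported selectively. The documents do not support it. These are supplementary tables, the main report is not among the documents, and nothing shows why the rows are absent.

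**Conclusion.** The point holds as a gap between the safety items that the protocol required and those that the appendix tables report. S10 lacks 2 of 13 solicited reactions, of which tachypnoea is the important one. Neither table has any of the required grades, and the absence of events does not account for the missing rows. As a result, the tables leave two questions open: whether measured tachypnoea differed between the arms, and whether a rhinorrhoea excess of about 25 percentage points was mild.

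It does not touch a primary result, since safety is not an endpoint, and it is not evidence of harm or of deliberate omission. The conclusion rests on the appendix being the only place where these data are tabulated; if they appear in the main report, a cross-reference is enough. The correction is worth making because it tabulates data that the protocol calls for.

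**What to change.** 1. In S10, add a tachypnoea row graded by the protocol's own cut-offs, and a nasal discomfort row or a footnote saying where it was coded.
2. In both S10 and S11, add a count of grade 2 or above for each event.
3. For the between-arm tachypnoea comparison, use respiratory rates from the day 7 visit, which both arms attend, with day 21 as a separate line. Label both as point prevalence at the visit, note the +7-day windows and the lack of a day 2 visit in controls, and give risk differences with 95% CIs.
4. Keep the present fever rows and show measured-fever grades beside them.
5. If respiratory rate was not recorded in controls after enrolment, say so and report tachypnoea for the vaccinated groups only.

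The cost is a little tabulation, with no new data collection if the measurements were made as the protocol states. The drawback is precision: with intervals about 3 to 7 percentage points either side at assumed rates of 2% to 10%, the tachypnoea comparison could exclude only a fairly large difference, and the table should not present it as showing more than that.

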## **110 Response to solicited local and systemic reactogenicity in children**

Any local or systemic reactogenicity (grade 1 or above) will be reviewed at the day 2 or 7 post-vaccine visits or as judged to be clinically indicated in the event a participants parent contacts the study team in the interim.

Any solicited local or systemic reactogenicity ongoing at day 7 will be documented as an adverse event and followed up according to clinical need. The frequency of follow-up in this case will be determined by the nature of the adverse event by a research clinician.

Any grade 3 local or systemic reactogenicity or a child with a fever ( $\geq 38^{\circ}\text{C}$ ) will be reviewed by a study clinician the same day or within 24 hours at the Sukuta Health Centre.

#### **111 Unsolicited safety data collection**

All AE will be classified according to their seriousness (section 7.1.2), severity (section 7.1.3) and relatedness to vaccination or azithromycin (section 7.1.4).

#### **112 Investigation of unsolicited adverse events**

Additional investigations undertaken if a child is unwell will be based on clinical judgment. However, any child with a fever of  $>38.5^{\circ}\text{C}$  beyond days 1 to 7 following vaccination will have a blood culture, a NPS (for respiratory virus diagnostic tests) and a malaria rapid diagnostic test performed.

#### **113 Verbal autopsies**

Following any maternal or infant death a verbal autopsy will be conducted using the latest WHO verbal autopsy form or applicable locally modified form. Autopsies are not otherwise performed in The Gambia and would not be considered to be culturally acceptable.

#### **114 Recording and coding of safety data including concomitant medication**

Prior to data entry and for the purposes of safety reporting all unsolicited AE will be classified using the Medical Dictionary for Regulatory Activities (MedDRA) (Version 18.0 or subsequent updates) according to System, Organ, Class (SOC), Preferred Term (PT) and Lowest Level Term (LLT).

Concomitant medication use will be documented using generic drug names and standardized administration routes and frequencies.

All data coded in this way will also have the AE/medication indicated in a free-text field for subsequent manual validation of the coded data.

#### **115 Safety reporting procedures**

SAE/IME will be reported by the PI to the sponsor and the local safety monitor within 24 hours of the investigator becoming aware. The report should be submitted on the designated SAE reporting form for the trial. The reports will be submitted by e-mail. Follow-up reports will subsequently be submitted as new information becomes available until the SAE/IME is closed or defined as ongoing (Section 7.1.2).

SAE/IME that are judged to be related to the study product but unexpected (SUSAR) will be reported by letter by the PI to The Gambia Government/MRC Joint Ethics Committee within 15 calendar days or within 7 calendar days if the event is fatal or life threatening. All SAE/IME will be reported by the PI to the Gambia Government/MRC joint ethics committee in the annual report

All SAE/IME will be reported to the Republic of the Gambia Medicines Control Agency by the sponsor according to the latest requirements of the agency.

All deaths occurring in the trial, irrespective of whether judged to be related, will be reported by the investigator by letter to the Gambia Government/MRC Joint Ethics Committee at their next meeting.

If new information becomes available that may alter the safety or conduct of the trial the investigator will inform the sponsor, the Local Safety Monitor, The Gambia Government/MRC Joint Ethics Committee and The Republic of the Gambia Medicines Control Agency in writing as soon as they become aware and generally within 5 calendar days.

SAE/IME that are judged to be related to the study product and unexpected (SUSAR) will be reported to SIIL by the sponsor via email, working closely with the PI.

All fatal or life threatening SUSAR will be reported to the Medicines Control Agency as soon as possible and within 7 calendar days of the sponsor becoming aware of the case. Other SUSAR will be reported as soon as possible and within 15 calendar days of the sponsor becoming aware of the case.

#### **116**    Safety database

All safety data required for pharmacovigilance will be captured in the clinical trial database developed for the trial (section 9.3). A separate pharmacovigilance database will not be used.

#### **117**    Pause rules

As there is robust safety data on the study vaccine Nasovac-S, as well as azithromycin, this study does not have any defined safety endpoints. However, the occurrence of any SUSAR will always result in a pause in recruitment. An evaluation will be made on whether the risk-benefit balance of the study has changed in light of the SUSAR. The decision on whether to continue the trial will be made by the sponsor, taking into account the information provided by the PI, the local safety monitor, the manufacturer (SIIL) and if necessary external experts (e.g. pharmacists). The sponsor's representative will collect all data and consult with MRC (the sponsor) head office prior to a decision being made.

